## Abstract

**Background:**

Children in foster care are at a higher risk for relationship problems than their counterparts raised by their biological family because of higher exposure to or prevalence of neglect or maltreatment early in life. Consequently, these children may also show more challenging behavior in their foster families, which in turn increases the parental stress experience of foster caregivers. Furthermore, the children may engage in a vicious cycle of risky relationship behaviors and expectations that put them at a greater risk for revictimization.

**Objective:**

To support foster caregivers in reducing the risk for revictimization, several intervention modules delivered via the internet were developed using a consumer-based approach (phase 1 of the multiphase optimization strategy). This project (phase 2 of the multiphase optimization strategy) aimed to develop a sustainable intervention by selecting promising intervention components based on their contribution to the outcome.

**Methods:**

In a 2^4^ factorial trial, a total of 317 foster caregivers with children aged 8 to 13 years are randomly assigned to 1 of 16 conditions. The primary outcome is the rate of revictimization from baseline to 3 months after intervention. Secondary outcomes include risk-taking and functional behaviors in relationships. All caregivers will receive access to all the intervention components after the follow-up assessment. The participants assigned to the condition with all component levels *on* are expected to show the best improvement in the primary and secondary outcomes.

**Results:**

Recruitment and data collection for the factorial trial started in March 2022 and is ongoing. As of October 2022, we recruited 181 families. Although it is difficult to predict the exact study timeline owing to COVID-19 pandemic–related delays, results are expected in February 2024.

**Conclusions:**

There is a need for easily accessible information related to raising children in foster care who have experienced early life adversities to interrupt the cycle of violence and enhance the developmental pathway of health and emotional stability. It might be useful, in addition to generally useful parenting information (eg, parental self-care or emotion regulation management), to specifically focus on the needs of these caregivers (eg, how to support the child to reduce dysfunctional relationship behaviors that may have developed because of early adverse experiences).

**Trial Registration:**

ClinicalTrials.gov NCT05235659; https://clinicaltrials.gov/ct2/show/NCT05235659

**International Registered Report Identifier (IRRID):**

DERR1-10.2196/38183

## Introduction

### Background

Exposure to potentially traumatic events and being bullied by peers or siblings in childhood constitute forms of victimization or revictimization, which may be associated with severe long-term effects on mental health [1-3], including anxiety, depression, or suicidality [4]. We include the experience of different forms of maltreatment (emotional, physical, and sexual abuse; neglect; and intimate partner violence) as well as bullying experiences in the definition of revictimization in this trial.

Given that childhood victimization leads to an increased vulnerability for subsequent revictimization in adolescence [5,6], findings highlight a strong need for evidence-based prevention programs targeting children with a history of maltreatment or bullying as a high-risk population for revictimization. Although all types of maltreatment in childhood were found to be associated with revictimization [7] and mental health, one study with adolescent girls in child welfare found that the emotional type of maltreatment showed the strongest link to revictimization in a cross-sectional study using self-report of the types of child maltreatment experienced [8]. However, when using a population sample, sexual maltreatment increased the risk for revictimization the most [7]. In a recent meta-analysis, Scoglio et al [9] identified the following risk factors in most studies on the association between sexual victimization and revictimization: risky sexual behavior, further maltreatment experiences in childhood, presence of posttraumatic stress disorder (PTSD), and emotional dysregulation. In contrast, protective factors have rarely been examined. Only parental caregiving was identified as a protective factor. Unfortunately, many of the included studies were cross-sectional, and it is not always clear which key mechanism is driving the link (eg, why the presence of PTSD is increasing risk).

### Children in Foster Care as an Example of a High-Risk Group for Revictimization

Children are often placed in foster care because of early adverse experiences in their family of origin, including maltreatment, with the majority experiencing neglect and emotional maltreatment, followed by physical and sexual abuse [10]. These children usually show comprehensive problems in relationships, including foster parent–child relationship, relationship with siblings [11], and peer relationships [12]. Furthermore, many children in foster care are affected by PTSD or attachment disorders [13] and show externalizing problem behaviors, which increase parental distress in (foster) parents [14]. The consequences of maltreatment (eg, PTSD-related symptoms and cognitions, such as negative self-appraisal; maladaptive cognitions of others and the world, eg, concerning the reliability and trustworthiness of others; and threat of harm) have been discussed to be causally involved in the risk for revictimization, although direct mediating effects were only established for threat of harm [15].

### Interventions to Support Foster Caregivers

Many parenting programs are designed to equip (foster) parents with strategies for increasing positive behaviors in their children and to support them in appropriately managing externalizing problem behavior [16]. Although parenting programs, in general, are a very promising approach to changing child behavior (via changed parenting behavior and reduced parental stress [17]), it has rarely been investigated whether parents may also help to lower the risk for revictimization in children with high risk due to adverse (early) childhood experiences. Warm and responsive parenting is associated with protective effects on children’s resilience to victimization [18], indicating that such parenting programs may be beneficial for coping with victimization and revictimization experiences. However, it is unclear whether parents could also be equipped with the knowledge and skills required to empower children with high risk for revictimization and thereby lower the risk for revictimizing experiences. Burke et al [19] outlined that *parental support* did not change the occurrence of victimization. Some authors also pointed out that some intervention components may be less effective than others in preventing or reducing child maltreatment experiences. Gubbels et al [20] concluded in their review and meta-analysis that “improving parental personal skills, improving problem-solving skills, and stimulating children’s prosocial behavior should not be the main focus of parental training programs for preventing and reducing child maltreatment” [20]. However, many of these have been identified as promising components to successfully change child externalizing behavior [21], suggesting that the 2 different outcomes may be the result of different pathways of change. Child externalizing problem behavior could be driven by engines different from the risk for revictimization. The intervention model theory of change is key to determining the best intervention components that are most likely to cause changes in the preferred outcome domain [22]. Furthermore, there is some evidence that also challenges the impact (foster) parents may have on the developmental adaptation of their children in care, and the dynamic and reciprocal processes between children and parents that build the foundation for many social learning–based parenting approaches have not been fully supported in a sample of children in foster care in the Netherlands [14]. Although the children’s behaviors affected the distress levels of the foster caregivers, the foster caregivers’ stress did not affect the children’s behaviors. Although this research group discussed a number of potential reasons for the lack of support for a transactional model (eg, foster parents may be expressing their distress less than biological parents, they could potentially give the child away, or children are less vulnerable to parental distress because they are accustomed to worse), this study may indicate that foster parent–child interactions may differ when children were maltreated in the past or at least the focus of the intervention may need to be shifted. For example, Burke et al [19] suggested teaching parents to “be more responsive and connected to their children when they are experiencing difficulties” [19] instead of equipping them with parent management skills more generally.

In sum, few evidence-based parenting programs for foster parents are available, and most of them include a package of intervention strategies [20] and require comprehensive training and parental participation (eg, in-home training as in Attachment and Biobehavioral Catch-up or Keeping Foster Parents Trained and Supported [23,24]). However, (foster) parent participation is challenging [25]. Furthermore, the intervention model and key drivers of change are not specifically tailored to the factors that put children with maltreatment experiences at a higher risk for future revictimization [26]. There is a clear need to identify behaviors and pathways that are responsible for revictimization [27] in this population.

### This Study

We use the multiphase optimization strategy (MOST) framework [22] to prepare and optimize an intervention for foster parents. The intervention components to be tested in phase 2 of MOST (this factorial study) were developed based on the phase 1 results. Multimedia Appendix 1 [27-32] provides a brief summary of the phase 1 results.

We built our conceptual model (Figure 1) and selected the following domains as targets for the intervention (*mediators* in the conceptual model):

Relationship-to-harm beliefs, which emphasize the degree to which a child believes that close relationships include harmThe threshold for risk detection, which, if lowered, leads to a delayed notice and, consequently, delayed response to danger cues in relationships

We combine these domains into 1 mediator called *relationship-related risk.*

A lack of relationship skills to build up and maintain positive and safe relationshipsDifficulties to detect safety signals and feeling emotionally secure in close relationships

We combine these domains into one mediator called *relationship-related safety.*

The emotional significance of a child’s origins and the child’s current foster family for *constructing a coherent identity*. This domain includes the recognition and sensitive responding of caregivers to the emotional significance of both families for the child’s identity development.

We developed promising intervention components and specified how we expect these to change the risks of revictimization experiences and their consequences.

**Figure 1 figure1:**
[figure not shown]
Conceptual model of the EMPOWERYOU intervention for primary caregivers of youth in care.

### Objectives and Hypotheses (for Phase 2 of MOST)

The primary aim of this study is to examine the effects of each candidate component developed based on the conceptual model and delivered via an internet-based prevention program to the primary caregivers of preadolescent youth in care on revictimization in the form of conventional crime, child maltreatment, peer and sibling victimization, sexual victimization, witnessing and indirect victimization, and cyberbullying. The ultimate goal is to choose the candidates that best reduce and prevent revictimization from a set of *4 components* with *2 levels each (on/off)*. The primary and secondary research objectives are presented in Textbox 1.

We will examine the hypotheses specified in Textbox 2, which are related to the *main effects of the intervention components* (3 content components and 1 adherence component).

Primary and secondary research objectives.
**Primary research**
**objectives**
To examine the efficacy of the selected candidate components on the primary outcome, the risk of revictimization, at follow-up (ie, 3 months after intervention; approximately 24 weeks after baseline)To examine the efficacy of the selected candidate components on the secondary outcomes (risk-taking behavior and functional behavior in relationships with the caregiver, siblings, peers, and others; Multimedia Appendix 2 [33-55] provides a full list of outcomes [[name], unpublished data, April 2021; [name], unpublished data, September 2021; [name], unpublished data, 2011; [name], unpublished data, April 2021; [name], unpublished data, August 2020; [name], unpublished data, March 2021]) at posttest assessment (ie, 1 week after intervention; approximately 12 weeks after baseline)
**Secondary research objectives**
To test the enduring effects of the selected components on the secondary outcomes at 3-month follow-upTo test the mediating effects of theory-driven factors (Multimedia Appendix 2 provides a full list of potential mediators) on the relationship between the selected components and the secondary outcomesTo explore whether there are any interaction effects between components on the primary or secondary outcomesTo conduct exploratory analyses of potential moderators

Hypotheses related to the main effects of the intervention components.
**Hypotheses to be examined**
Component *Watch Out!* deals with relationship-related risks, and we hypothesize that receiving this component will result in a better detection of risk signals in relationships and less risk-taking cognitions. This will lead to less relationship-related risk-taking behavior, which, in turn, will result in reductions in revictimization experiences and other secondary outcomes.Component *You are safe here* deals with relationship-related safety, and we hypothesize that receiving this component will result in a better detection of relationship-related safety signals in relationships and more emotional security. This will lead to more functional relationship behavior, which, in turn, will result in reductions in revictimization experiences and other secondary outcomes.Component *Who am I and where do I belong?* deals with the construction of identity, and we hypothesize that receiving this component will increase parental support for the child’s efforts in constructing a coherent identity. This will lead to less risk-taking behavior and more functional relationship behavior, which, in turn, will result in reductions in revictimization experiences and other secondary outcomes.Component *My Coach* deals with professional support, and we hypothesize that professional support from a parent coach who is facilitating each component will result in higher program adherence or engagement, which will yield larger intervention effects on the primary and secondary outcomes than without professional support.We hypothesize that there will be an interaction effect between the relationship risk and relationship safety components. When both components are present, the effect will be larger compared with when only one of them is present.We hypothesize that there will be an interaction effect between each component and the professional support component such that with professional support, the effects of each component will be larger than those without professional support via greater adherence of the caregiver.

We will also answer the following four questions to establish how well the conceptual model captures the relevant mechanisms of the intervention (mediation analyses, adapted from the study by Smith et al [56]): how well will the three mediators (relationship-related risk, relationship-related safety, and constructing an identity) predict the occurrence of revictimization, how well does each module content (*Watch Out*!, *You are safe here*, and *Who am I and where do I belong*?) and the coach evoke each of the 3 mediators, how much of the relationship between the intervention’s content components and revictimization is explained by the 3 hypothesized mediators, and how much variability between the content components and revictimization will remain unexplained.

Furthermore, the following variables were identified as potential moderators of intervention (component) efficacy based on the literature review in phase 1:

Child executive functioning (ie, an impaired “ability to shift, inhibit, and focus attention; maintain focus in the face of distracting information” [28]): Reduced executive functioning will lead to smaller intervention effects.Gender of the child [27,57]: We expect worse outcomes in girls than boys.Type of maltreatment [7-9]: Sexual maltreatment experiences will lower the intervention effect compared with other types.Contact with the family of origin [58]: We assume that conflictual contact may reduce intervention effects.Caregiver’s history of child maltreatment [59]: We expect caregivers with such a history to benefit less from the intervention.

Taken together, we use the MOST framework [22] to optimize a web-based program for foster parents, which comprises 4 intervention components. To optimize the program, the primary aim of this study is to examine the efficacy of each component on the primary and secondary outcomes. This paper outlines the protocol (version 01) or the factorial trial, following the SPIRIT (Standard Protocol Items: Recommendations for Interventional Trials) guidelines for clinical trials (Multimedia Appendix 3 provides the SPIRIT checklist).

## Methods

### Ethics Approval

This study is conducted in accordance with the Declaration of Helsinki. This study was approved on September 1, 2021, by the University of Bremen Ethics Committee (no. 2021-09). Any changes to this protocol will be submitted to the institutional review board for notification and approval.

### Study Design

The EMPOWERYOU project (funded by the German Ministry of Education and Research, Project code FKZ 01KR1806D) aims to develop and optimize a web-based parenting program by using the MOST framework [22]. This study will use a 2×2×2×2 full factorial design by randomly allocating participants to 1 of 16 experimental conditions (Table 1). To estimate the main effects of the 4 intervention components and their interactions, data from all the experimental conditions will be used. For example, the effect of the component *Relationship-related risk* will be estimated by comparing the mean of the experimental conditions 1 to 8 with the mean of the conditions 9 to 16 (Table 1). Families in the first condition will not receive any experimental component but will be delivered the 2 basic intervention modules that every caregiver receives. Families will be informed that everyone may access all modules and that the sequence and timing of each module will be based on a randomization procedure.

**Table 1 table1:** Experimental intervention conditions (optimization schema).

Experimental condition	Component 1: *Watch Out*!—relationship-related risk	Component 2: *You are safe here*—relationship-related safety	Component 3: *Who am I and where do I belong?*—identity	Component 4: *My Coach*—professional support
1	Off^a^	Off	Off	Off
2	Off	Off	Off	On^b^
3	Off	Off	On	Off
4	Off	Off	On	On
5	Off	On	Off	Off
6	Off	On	Off	On
7	Off	On	On	Off
8	Off	On	On	On
9	On	Off	Off	Off
10	On	Off	Off	On
11	On	Off	On	Off
12	On	Off	On	On
13	On	On	Off	Off
14	On	On	Off	On
15	On	On	On	Off
16	On	On	On	On

^a^Not included in the intervention.

^b^Included in the intervention.

### Sample Size Calculations

Anticipated effect sizes were estimated from the reported effect sizes for victimization and revictimization interventions, which also included (1) facilitating risk detection skills; (2) social skills, such as problem-solving or conflict management; (3) skills to build healthy relationships; and (4) the ability to reflect on own expectations that relationships will include harm [28,60,61]. We expect small to moderate effect sizes between Cohen *d*=0.28 and Cohen *d*=0.46 for the main effects of specific intervention components (component 3: 0.46, component 4: 0.28, and component 6: 0.32). Thus, a sample size of 317 was determined as necessary to detect the smallest anticipated effect size of Cohen *d*=0.28. To detect this difference with the analysis of covariance as the suggested method for component selection by the developer of the factorial design (groups=2, *df*=1, covariate=1) with 80% power at α=.10 per intervention component or interaction, a sample size of 317 is required (calculated with FactorialPowerPlan SAS Macro provided by [name] [62]). We will use an intention-to-treat approach, although only one family dropped out during the intervention period in the pilot study. In contrast, findings from the pilot study showed that 26% (4/15) of the recruited caregivers that registered for the website dropped out before the intervention. Therefore, we consider a dropout rate (before the allocation to condition) of 26%. Therefore, we aim to recruit a total of 429 families. Recruitment will be stopped as soon as we reach the sample size needed for the analysis (N=317).

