### Statistical Analysis

#### Analyses

Before the analyses, missing data will be examined and appropriately handled using multiple imputation or full information maximum likelihood estimation. To investigate the effectiveness of each intervention component, the primary analyses will test the pre–follow-up change in children’s revictimization composite scores. The primary analysis will be conducted in an intention-to-treat sample. We will use the analysis of covariance with main and interaction effects on the primary and secondary end points. The main effects and interactions are estimated based on aggregates (each reflecting the presence or absence of a specific component) across the 16 experimental conditions. The main effects will be modeled as a fixed effect with baseline levels of an outcome as a covariate and an assumed type I error of *P*<.10 (recommended for component selection [22]). To examine the hypotheses related to mediating and moderating effects, we will use regression analyses. Mediational analyses will be conducted by analyzing the indirect effects of each component on the primary outcome via the assumed mediators (Figure 1). Moderator analyses will be modeled in steps with baseline predictors (eg, type of maltreatment) and then as a second model including interactions with the main effect by condition.

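### The 80% power at d=0.28 requires 317 observed week-24 outcomes, but only 317 families are randomised and no loss after allocation is allowed for

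*Protocol article*

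**What the plan says.** The Sample Size Calculations section of the protocol article fixes the target for the smallest of three anticipated main effects (0.28, 0.32 and 0.46): "a sample size of 317 was determined as necessary to detect the smallest anticipated effect size of Cohen *d*=0.28". The test is an analysis of covariance described as "groups=2, *df*=1, covariate=1", and the claim is that "with 80% power at α=.10 per intervention component or interaction, a sample size of 317 is required".

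On loss, the section says that "only one family dropped out during the intervention period in the pilot study" and makes no numerical allowance for it. The only allowance is for an earlier stage: "we consider a dropout rate (before the allocation to condition) of 26" per cent. This raises recruitment to 429 families. The section then states: "Recruitment will be stopped as soon as we reach the sample size needed for the analysis (N=317").

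The Methods paragraph of the abstract gives the same figure as the number allocated: "a total of 317 foster caregivers with children aged 8 to 13 years are randomly assigned to 1 of 16 conditions". The primary outcome is measured about 24 weeks after baseline (primary research objectives). The Analyses section plans an intention-to-treat analysis with multiple imputation or full information maximum likelihood.

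**The concern.** One figure, 317, does two jobs: it is the number of outcomes the power calculation needs and the number of families randomised. The two agree only if every randomised family provides a week-24 outcome. That outcome comes from a web questionnaire three months after the intervention ends. The pilot already lost a family during the intervention period, and no pilot result is quoted for the follow-up period.

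At stake is the first step of the Decision-making Process section, which looks for a significant main effect on the primary outcome at follow-up, tested at P<.10. If fewer than 317 outcomes are observed and nothing makes up the difference, a component with a true effect of 0.28 misses that step more often than the 20% implied by the stated power.

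**Working it through.** **Inputs from the protocol article.** d = 0.28 (also 0.32 and 0.46); alpha = .10; power 80%; 1 numerator degree of freedom; one covariate with no correlation stated; 317 randomised; 26% dropout before allocation; 429 recruited. Each component is on in 8 of the 16 conditions, so its two levels are equal in size.

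**Inputs assumed.** The article gives no rate of loss from allocation to week 24. I use 5%, 9%, 20% and 30%. The 9% is 1 of 11 pilot families, where 11 = 15 − 4 is inferred from the pilot counts. Its exact 95% interval is 0.2% to 41%, so it carries little weight. The other three rates are illustrative.

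**Step 1: reproduce 317.** For two equal groups with N observed outcomes, the F test has noncentrality N × d²/4 = N × 0.0196.

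- N = 316: noncentrality 6.194, power 0.7991.
- N = 317: noncentrality 6.213, power 0.8002.

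So 317 is the smallest N that reaches 80%, with a two-sided test, no variance reduction from the covariate and no loss. By the normal approximation, one-sided alpha .10 would need 230 and two-sided alpha .05 would need 402. Neither matches.

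**Step 2: reproduce 429.** 317 / (1 − 0.26) = 428.4, rounded up to 429. In the other direction, 429 × 0.74 = 317.5. The whole increase is used up before allocation, leaving about 317 to randomise and no margin afterwards.

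**Step 3: power with 317 randomised, by loss to week 24, no covariate credit.** Observed n = 317 × (1 − loss).

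| Loss | Observed n | Power, d=0.28 | Power, d=0.32 | Power, d=0.46 | Detectable d at 80% power |
|---|---|---|---|---|---|
| 0% | 317 | 80.0% | – | – | 0.28 |
| 5% | 301 | 78.2% | 87% | 99% | 0.29 |
| 9% | 288 | 76.6% | 86% | 99% | 0.29 |
| 20% | 254 | 71.9% | 82% | 98% | 0.31 |
| 30% | 222 | 66.8% | 77% | 96% | 0.33 |

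**Step 4: what the baseline covariate could recover.** If d is expressed on the unadjusted standard deviation, a baseline-outcome correlation r divides the residual variance into the signal, so noncentrality becomes n × 0.0196 / (1 − r²). Power returns to 80% when n / (1 − r²) is about 317:

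- 9% loss: 1 − r² = 288/317 = 0.909, r ≈ 0.30.
- 20% loss: 1 − r² = 254/317 = 0.801, r ≈ 0.45.
- 30% loss: 1 − r² = 222/317 = 0.700, r ≈ 0.55.

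With r = 0.5, power at d=0.28 would be about 86%, 82% and 78% at 9%, 20% and 30% loss. With r = 0.3 it would be about 80%, 75% and 70%.

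**The case against.** The strongest reply is that post-allocation loss was considered and judged small. The section mentions the single pilot loss alongside the intention-to-treat approach and contrasts it with the much larger loss before allocation. That is a disclosed judgement. However, it covers the intervention period only, and the calculation still treats the loss as zero.

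A second reply is that intention-to-treat with imputation or full information maximum likelihood keeps all 317 in the analysis. It does keep them in the analysis set. Week-12 data and the child report may also recover part of the missing information, but full recovery cannot be expected, so 317 randomised families with gaps are not worth 317 observed outcomes.

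A third reply is that the covariate may more than compensate. This stands as a possibility: at r = 0.5 and 20% loss, power exceeds 80%. A reader might infer from the concern that the true power must be below 80%. The documents do not support that, because they give neither the correlation nor the loss. Equally, they do not use the covariate to justify 317, which reproduces only without it.

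A reader might also infer that components missing p<.10 are discarded. The Decision-making Process section does not say so: a component without a significant main effect is next considered for interactions and then through the mediation models. Nor are all components affected alike. Of the three with a stated effect, only the one at 0.28 falls below 80% at losses up to 20%.

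**Conclusion.** The point holds as a mismatch between what the power calculation needs and what the recruitment rule delivers. Neither 317 nor 429 is miscalculated. As calculated, the stated 80% belongs to 317 observed week-24 outcomes, and the plan randomises 317 with no allowance for later loss.

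The size rests on assumed loss. For d=0.28 without covariate credit, the shortfall is under 2 percentage points at 5% loss, about 3 at the pilot-like 9%, 8 at 20% and 13 at 30%. The consequence is a higher chance that the weakest anticipated component fails the first selection step, for example 28% instead of 20% at 20% loss. A moderate baseline-outcome correlation could remove the shortfall, so the direction of the net effect is open until the plan states both quantities.

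**What to change.** In the Sample Size Calculations section:

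- State that 80% power at d=0.28 refers to 317 families with an observed week-24 outcome.
- Give the power, or the detectable d, for 317 randomised at the loss the investigators expect. Without covariate credit this would be, for example, 77% at 9% or 72% at 20%.
- If the baseline covariate is relied on to offset the loss, state the baseline-outcome correlation assumed and whether d is on the unadjusted scale.

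The cost is a sentence or two and a slightly less favourable stated power. No extra families are needed, and the design and analysis do not change.
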